##### Tokens

As participants progress through Peer Tree, they will receive tokens on the home screen. Participants will earn tokens depending on their interaction with the application. For instance, if participants have posted a certain number of posts in the chat forum, they will earn a token.

##### Chat forum

Users of Peer Tree also have access to a moderated chat forum where they can discuss each module with their peers. A one-on-one chat function is also available for participants to contact other participants or moderators privately. There are four types of moderation in the peer tree study, all of which are in place to ensure participant safety. These include clinical, peer, research, and technical moderation.

##### Moderation manual and training

A training manual has been developed detailing the responsibilities and duties of each kind of moderator (detailed below) as well as the protocol for managing serious adverse events and risk issues. This manual will be used as a reference for all moderators and the research team throughout the trial. The research team and peer moderator will undergo training in administering the Structured Clinical interview for Diagnostic and Statistical Manual for Mental Disorders (DSM-5)–research version (SCID-5-RV) and assessing and managing risk and this will be conducted by the principal investigator (PI) who is a registered clinical psychologist. The PI will only permit someone to be part of the research or moderation team once they received training on identifying and managing risk and demonstrate competence on following the risk protocol procedures.

##### Clinical moderation

A mental health professional with experience in recognising potentially dangerous or risky behaviour will monitor the chat forum. If a clinical risk (e.g. intention to harm self or others) is detected, the clinical moderator will follow up directly with the young person and aid as necessary. Clinical moderators will monitor the forums every day. See Supplementary material for the standardised operating procedure on reporting identifiable risks.

##### Peer moderation

A peer with similar demographics to the participants will be hired to act as a peer moderator on the chat forum. The role of the peer moderator will be to engage the participants and facilitate discussion on the forums. If the peer moderator identifies any potentially dangerous or risky behaviour, they will notify the clinical moderator directly. The peer moderator will be active every day with the exception of weekends.

##### Research moderation

The research team will moderate the forums daily to ensure the intervention is running smoothly and to assist with any inquiries. Research moderators will also engage with participants in the forums. If any research moderators identify any potentially dangerous or risky behaviour, they will notify the clinical moderator directly. Research moderators will be active every day.

##### Technical moderation

There is an automated keyword function embedded within the smartphone application that is activated each time a participant posts a contribution containing potentially offensive words. Any participant who tries to use one of these words or phrases will be blocked from doing so and a notification will be sent to the research team. The research team or clinical moderator will assess the notification and follow up on the issue if necessary.

##### Weekly check-ins

Each week, a member of the research team will call the participant for a short conversation about their progress, any technical issues experienced, and to answer any of their questions.

### Strategies to improve adherence to interventions {11c}

A weekly phone check-in will be completed by a member of the research team for the duration of the intervention. During this check-in, the researcher will answer any questions the participants have and encourage them to engage with the content and chat forum if they are not currently.

### Relevant concomitant care permitted or prohibited during the trial {11d}

All participants will be able to continue or commence any mental health or psychological care as required.

### Provisions for post-trial care {30}

This study does not deal with a clinical population. All participants are screened using a semi-structured clinical interview to ensure they do not meet the criteria for a psychiatric illness. Thus, any participant accepted into the programme is unlikely to require post-trial care. Once the trial is completed, there is no further follow-up. The exception to this is if a participant is withdrawn from the study due to a deterioration in mental health. In this case, we will follow up with the participant to ensure they are receiving adequate support.

### Outcomes {12}

See Table 1 for the SPIRIT schedule of measures used in this study. The primary outcomes are loneliness, acceptability, feasibility, and safety of Peer Tree. Secondary outcomes include social anxiety, depression, quality of life, and psychological well-being. Demographic variables will include age, gender, sexuality, ethnicity, work status, level of education, previously attempted university degrees, current university course load, postcode, and religion.

**Table 1 Tab1:** SPIRIT schedule of outcome measures

Outcome measures	Baseline	End of treatment	Follow-up
Enrolment			
Eligibility screen	X		
Informed consent	X		
Allocation	X		
Assessments			
Demographic form	X		
UCLA-LS3	X	X	X
SIAS	X	X	X
CES-D	X	X	X
LSNS-18	X	X	X
IIP-32	X	X	X
PWB-54	X	X	X
PANAS-SF	X	X	X
WHO QOL-Bréf	X		
COVID-19 question	X	X	X
Adherence		X	
Mean Peer Tree application acceptability		X	
Mean Peer Tree application feasibility		X	
Mean Peer Tree application usability		X	

*UCLA-LS3* UCLA Loneliness Scale-Version 3, *SIAS* Social Interaction Anxiety Index, *CES-D* Centre for Epidemiological Studies-Depression, *LSNS* Lubben Social Network Scale, *IIP-32*, Inventory of Interpersonal Problems, *PWB* Scales of Psychological Wellbeing, *PANAS-SF* Positive and Negative Affect Scale–Short Form, *WHO QOL-Bréf* World Health Organization Quality of Life-Bréf

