**Methods:**

This will be a pilot randomised controlled trial (RCT) comparing a strength-based digital smartphone application (Peer Tree) with a control condition. Forty-two young people enrolled at university will be recruited for this pilot RCT. Participants with suicidal ideation or behaviours, acute psychiatric symptoms in the past month, or a current diagnosis of a mood or social anxiety disorder will be excluded. Allocation will be made on a 1:1 ratio and will occur after the initial baseline assessment. Assessments are completed at baseline, at post-intervention, and at follow-up. Participants in the control condition complete the same three assessment sessions. The primary outcome of the study will be loneliness. Depression, social anxiety, quality of life, acceptability, usability, feasibility, and safety of Peer Tree will also be measured as secondary outcomes.

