## Objectives {7}

The objective of this study is to evaluate the acceptability, feasibility, safety, and initial efficacy of a positive psychology smartphone application intervention called Peer Tree. Peer Tree is a digital smartphone intervention targeting loneliness and is a new iteration of our previous application +Connect. Peer Tree includes many features from +Connect [30, 31] but also includes the personalisation of modules based on user symptom profiles, a peer- and clinician-moderated chat forum, and animated videos to address loneliness in young people using a positive psychology framework.

It is hypothesised that Peer Tree participants, compared with the control participants, will report significantly lower loneliness at post-intervention, and these effects will remain at follow-up. It is also anticipated that Peer Tree participants, compared with control participants, will report significantly lower social anxiety and depressive symptoms, and higher quality of life and well-being outcomes at post-intervention as well as at follow-up.

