##### World Health Organisation Quality of Life (WHO QOL-BRÉF; [44])

The WHO QOL-BRÉF is a 26-item abbreviated version of the WHO QOL-100, a quality-of-life assessment which is cross-culturally valid. The WHO QOL-BRÉF contains one item from each of the 24 facets of quality of life in the WHO QOL-100, plus two additional items on the overall quality of life and general health. The WHO QOL-BRÉF has four domains of quality of life: physical health, psychological, social relationships, and environment. The domains physical health, psychological, and environment have good internal consistency (*α* = .82, .81, .80 respectively) and the social relationship domain has acceptable internal consistency (*α* = .68) [45].

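### Quality of life is hypothesised to differ between arms at post-intervention and follow-up, but Table 1 schedules its only instrument at baseline, so the hypothesis cannot be tested as planned

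*Protocol article*

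**What the plan says.** Three places in the protocol article treat quality of life as an outcome.

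- Objectives {7} predicts, for Peer Tree compared with control, "higher quality of life and well-being outcomes at post-intervention as well as at follow-up".
- Outcomes {12} reads: "Secondary outcomes include social anxiety, depression, quality of life, and psychological well-being". Quality of life and psychological well-being are named as separate items.
- The Methods paragraph of the Abstract reads: "Depression, social anxiety, quality of life, acceptability, usability, feasibility, and safety of Peer Tree will also be measured as secondary outcomes".

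The instrument is described among the secondary outcome measures: "The WHO QOL-BRÉF is a 26-item abbreviated version of the WHO QOL-100, a quality-of-life assessment which is cross-culturally valid". No other quality-of-life measure appears in the article.

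Table 1 in Outcomes {12} is the schedule of measures. Its WHO QOL-Bréf row has a mark under baseline and blanks under end of treatment and follow-up.

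**The concern.** The hypothesis compares the arms at two visits after randomisation. The schedule collects the measure once, before randomisation. These cannot both be right. If the table governs conduct, a stated directional hypothesis has no data behind it, and the planned group-by-time model has nothing to fit for this outcome. If the text governs, the published schedule is wrong, and a reader of the results could not confirm that later quality-of-life scores were planned.

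**Working it through.** No statistical formula applies. The check sets the relevant statements side by side and counts scheduled visits.

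**Step 1. What the hypothesis needs.** Objectives {7} requires a between-arm comparison at post-intervention and another at follow-up, so two contrasts, each needing scores from both arms at that visit.

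**Step 2. What the schedule supplies.** Marks in Table 1:

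| Measure | Baseline | End of treatment | Follow-up | Marks |
|---|---|---|---|---|
| UCLA-LS3 | X | X | X | 3 of 3 |
| SIAS | X | X | X | 3 of 3 |
| CES-D | X | X | X | 3 of 3 |
| LSNS-18 | X | X | X | 3 of 3 |
| IIP-32 | X | X | X | 3 of 3 |
| PWB-54 | X | X | X | 3 of 3 |
| PANAS-SF | X | X | X | 3 of 3 |
| COVID-19 question | X | X | X | 3 of 3 |
| WHO QOL-Bréf | X | – | – | 1 of 3 |

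The remaining assessment rows are single-visit by nature: demographics at baseline, and adherence and the app ratings at end of treatment. The IIP-32 and the COVID-19 item, which the article classes as covariates, are scheduled more often than this hypothesised outcome.

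**Step 3. Can the baseline score serve?** The Abstract says allocation "will occur after the initial baseline assessment". The single scheduled score therefore precedes treatment, and any arm difference in it is chance imbalance.

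**Step 4. Can another measure serve?** The PWB-54 is given three times, but both Objectives {7} and Outcomes {12} list well-being in addition to quality of life, and the two instruments are described separately. It cannot stand in.

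**Step 5. Are the visits available?** Yes: "Assessments are completed at baseline, at post-intervention, and at follow-up". The sessions exist; only the form is missing from two of them.

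**Step 6. Size.** The sample size from Sample size {14} is 42.

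- Post-baseline records needed, with full retention: 42 × 2 = 84.
- Post-baseline records scheduled: 42 × 0 = 0.
- Hypothesised contrasts that can be estimated: 0 of 2.

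**Step 7. Effect on the model.** Statistical methods {20a} uses a repeated factor with levels baseline, post-intervention and follow-up. With one level observed, there is no change over time and no group-by-time term for quality of life.

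**The case against.** The strongest reply is that two marks were simply left out of the table. The prose consistently treats quality of life as a measured outcome, against two blank cells. Table 1 is also loosely matched to the text elsewhere: it has no row for safety, and it labels the affect and well-being scales differently from their descriptions. An omission is at least as plausible as a deliberate baseline-only design. This stands as an explanation, and it makes the finding conditional: the hypothesis is untestable if the schedule is followed as printed. It does not remove the contradiction, because nothing in the article says the form is repeated.

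A second reply is that a journal article condenses the full protocol. That would excuse missing detail. Here both the hypothesis and the schedule are printed and they disagree, and no analysis plan can recover scores that were not scheduled. A reading fault in the table is also unlikely, since the rows on either side are complete.

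A third reply is that one secondary outcome in a 42-person pilot is a small matter. The reach is indeed limited: loneliness, the sample size, acceptability, feasibility and safety are untouched. Within that reach, though, the loss is total.

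**Conclusion.** The concern holds. The printed schedule yields no quality-of-life data after randomisation, so neither of the two hypothesised contrasts can be estimated (0 of 84 possible records). This rests on Table 1 being followed as printed; the 84 also assumes all 42 participants attend both later visits. If the form was in fact given at every session, the error lies in the table alone and no data are lost. In either case the article contradicts itself on a stated hypothesis and must be corrected. The primary analysis is not affected.

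**What to change.** First, state at which visits the WHO QOL-BRÉF was actually administered. Trial status says collection had begun and was expected to finish by June 2021, so the answer decides which of these applies.

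1. **Given at all three visits.** Add the two missing marks to Table 1. The cost is a table correction.
2. **Not given so far, but visits remain.** Add the marks and give the form at end of treatment and follow-up to everyone still to be seen. The cost is one 26-item questionnaire at two existing sessions. Report that the data cover later participants only. Define that subset by date of randomisation, not date of visit: under Participant timeline {13}, Peer Tree participants wait to be onboarded and controls do not, so a cut-off on visit date would select the arms differently.
3. **Not given and no visits remain.** Remove quality of life from the hypotheses and secondary outcomes in the Abstract, Objectives {7} and Outcomes {12}, and describe the scale as a baseline characteristic. The text change is small, but it withdraws a stated outcome after data collection began. It should go through the ethics and registry route in the amendments section {25}, and the trial report should say that the outcome was planned and not collected.

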#### Primary outcome

##### UCLA Loneliness Scale-Version 3 (UCLA-LS; 36)

The UCLA-LS is a 20-item measure employing a 1 (never) to 4 (always) ordinal scale [34]. The measure consists of both positively and negatively worded items that assess loneliness (e.g. How often do you feel that you are no longer close to anyone?). The UCLA-LS has been shown to correlate negatively with life satisfaction and perceived social support, thus supporting its convergent validity with related constructs [35].

#### Secondary outcomes

##### Centre for Epidemiological Studies-Depression (CES-D; 38)

The CES-D is a 20-item self-report measure of depressive symptoms, which employs a 0 (rare or none of the time) to 3 (most or all of the time) Likert-type scale. Scores are summed to create a total score indicative of depression symptomatology, where higher scores indicate the presence of more symptomatology. The CES-D has strong internal reliability [36]. The CES-D has strong internal consistency ranging from *α* = .88 to .90 across time [37].

##### Social Interaction Anxiety Index (SIAS; 39)

The SIAS is a 20-item measure employing a 0 (not at all characteristic of me) to 4 (extremely characteristic of me) Likert-type scale. The 17 straightforward items (i.e. items that are not negatively worded) will be used here as they have previously been deemed more reliable than the full 20-item measure [38]. The measure involves statements describing one’s thoughts, feelings, and behaviours to social situations. The SIAS has demonstrated excellent internal consistency (*α* = .88 to .93; *α* = .88 to .93) [38, 39].

##### Lubben Social Network Scale (LSNS; 41)

The LSNS is an 18-item scale that assesses the frequency and quality of social contact—such as talking about private matters—in an individual’s network. There are three subscales, each consisting of 6 items relating to family, neighbour, and friend social ties. The scale employs a 0 (none) to 5 (nine or more) Likert scale and includes 6 items (e.g. How many relatives do you see or hear from at least once a month?) which are summed together to provide a total score. Higher scores indicate larger social networks and lower risk of social isolation. The scale has demonstrated adequate levels of internal consistency (*α* = .93 for the total LSNS) and the proposed clinical cut-points showed good convergent validity [40].

##### The Scales of Psychological Well-Being (SPWB; 42)

The SPWB is a 54-item questionnaire that measures psychological well-being across six dimensions: autonomy, positive relations with others, environmental mastery, personal growth, purpose in life, and self-acceptance. Items are scored on a 6-point Likert scale from 1 (strongly disagree) to 6 (strongly agree). This widely used scale has demonstrated good internal consistency and construct validity [41]. Internal consistency for the SPWB ranged from *α* = .81 to .87. We will use an overall SPWB score by adding the scores for each subscale.

##### The Positive and Negative Affect Schedule (PANAS-10; 43)

The PANAS-10 is a 10-item subscale measure of the PANAS scale. The measure asks respondents to rate the extent to which they feel a particular emotion along a 5-point Likert scale ranging from 1 (very slightly) to 5 (extremely). This subscale measure has been shown to have good internal consistency (*α* = .88) [42]; and acceptable levels of convergent validity [43].

##### World Health Organisation Quality of Life (WHO QOL-BRÉF; [44])

The WHO QOL-BRÉF is a 26-item abbreviated version of the WHO QOL-100, a quality-of-life assessment which is cross-culturally valid. The WHO QOL-BRÉF contains one item from each of the 24 facets of quality of life in the WHO QOL-100, plus two additional items on the overall quality of life and general health. The WHO QOL-BRÉF has four domains of quality of life: physical health, psychological, social relationships, and environment. The domains physical health, psychological, and environment have good internal consistency (*α* = .82, .81, .80 respectively) and the social relationship domain has acceptable internal consistency (*α* = .68) [45].

##### Peer tree acceptability

Acceptability will be assessed in the same way as our previous pilot trials see [32, 33]. Acceptability will be assessed post-intervention using satisfaction ratings on application enjoyment and usefulness and content helpfulness. A set of 22 satisfaction ratings will be measured using a 5-point Likert scale from 1 (*extremely disagree*) to 5 (*extremely agree*), with an example item being ‘I enjoyed using the app’. A further 15 satisfaction ratings were adapted from Meyer et al. (2012) and involve participants making ratings on a 3-point Likert scale from 0 (*not at all satisfied*) to 2 (*very much so*), an example item being ‘Did the intervention help you to feel more connected with others?’ [31]. Finally, participants will be asked to rate how helpful they found each Peer Tree module (e.g. gratitude) on a 4-point Likert scale from 1 (*not at all helpful*) to 4 (*very helpful*).

##### Peer tree feasibility

Feasibility will be assessed by considering four key factors: uptake, attrition, retention, and application completion. Uptake is defined as the number of potentially eligible young people who attended the baseline assessment. We set an apriori threshold of at least 50% of people who were eligible would attend a baseline assessment. Attrition is defined as the number of participants who attended the baseline assessment but failed to log into the app for more than three consecutive days and where researchers were unable to contact the participant. We set a priori threshold of a 30% attrition rate. Retention is defined as the number of participants who complete the intervention. Application completion is defined as accessing and completing at least 50% of the app (21 out of 42 days) within the maximum allocated time of 8 weeks. These criteria are consistent with our previous pilot trials of +Connect [32, 33].

##### Peer tree safety

Safety is operationalised as the incidence of serious adverse events during the course of the study as a result of the Peer Tree intervention. Serious adverse events are defined in this trial as harm to self (including non-suicidal self-injury and suicide), risk of harm to others (including homicidal risk), and risk of harm to objects or property. Adverse events will be actively assessed and monitored throughout the intervention and managed accordingly as described in the risk assessment protocol located within the Supplementary files. The intervention will be deemed safe if there are no reported adverse events related to the trial.

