## Methods

### Trial design {8}

Peer Tree is a pilot randomised controlled trial utilising a parallel groups design where participants are randomly allocated to either the Peer Tree intervention or control (i.e. No Peer Tree) group. There will be no blinding in this trial for assessors. Once determined to be eligible during the baseline assessment, participants will be randomised to one of the two conditions. Participants in both groups will complete a post-intervention assessment 6 weeks after the baseline or once they have finished the intervention. Participants in the Peer Tree arm will be given a maximum of 8 weeks to complete the smartphone application, after which they will complete the post-intervention assessment. Participants will then complete a follow-up assessment 3 months after the post-intervention assessment. Figure 1 displays the Consolidated Standards of Reporting Trials (CONSORT) flow diagram of the study procedure. The protocol was designed in accordance with the Standard Protocol Items: Recommendations for Interventional Trials (SPIRIT) and Good Clinical Practice Guidelines.

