### Plans to promote participant retention and complete follow-up {18b}

Participants in the intervention will be contacted weekly for the duration of the trial to promote engagement and retention through the intervention. Participants in control will be contacted 2 weeks before each assessment to schedule the next assessment. A reminder will be sent via text message a day prior to the assessment.

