### Adverse event reporting and harms {22}

An adverse event within this study is defined as participants reporting more than discomfort (e.g. distress) over a particular aspect of the current study. Participants are screened for clinical risk of harm to self, others, and objects or property during the phone screen and during each of the assessments.

Due to the nature of the smartphone application content, we anticipate minimal risk to participants. Participants will not be coerced into answering questions or asked to contribute if they feel uncomfortable, and they can choose not to answer any questions in the packet of measures at the assessment sessions. Participants will be able to withdraw their participation in the smartphone application intervention at any time. We have included a contact section in the smartphone application where there will be information about referral options to a national crisis service.

In the unlikely event of any participant experiencing significant ongoing distress during their participation, the researchers will actively assist the participant in obtaining any additional support they may require. Our protocol for doing this is to provide contact numbers for a national crisis service and/or the University Counselling Service and prioritising the person accessing support from services in their local area that can be most responsive to their needs. The researchers will support the person in getting in touch with their desired health services (e.g. local GP) or offer to do so on their behalf. This will only be done with their permission. In the unlikely scenario that a participant is unwilling for services to be contacted and the person presents a risk to themselves or others, the researchers will have a duty of care to contact services without the person’s permission. This possibility is highlighted in the participant information sheet. The PI is responsible for evaluating all adverse events in the trial and reporting all relevant details to the local ethics committee and mental health service.

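### Safety is defined over the whole study, but active assessment is stated only for the intervention period and between-visit monitoring is described only for app users

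*Protocol article*

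**What the plan says.** The Peer tree safety section gives the outcome: "Safety is operationalised as the incidence of serious adverse events during the course of the study as a result of the Peer Tree intervention". Further on, the same paragraph gives the active collection period: "Adverse events will be actively assessed and monitored throughout the intervention and managed accordingly". The events are self-harm (with non-suicidal self-injury and suicide included), risk of harm to others, and risk of harm to objects or property. The app is declared safe if no trial-related adverse event is reported. Outcomes {12} lists safety among the primary outcomes, while the Abstract places it among the secondary ones.

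The study outlasts the intervention. Participants have at most 8 weeks for the app, and Trial design {8} continues: "Participants will then complete a follow-up assessment 3 months after the post-intervention assessment".

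Adverse event reporting and harms {22} adds a second source: "Participants are screened for clinical risk of harm to self, others, and objects or property during the phone screen and during each of the assessments". According to the Abstract, controls attend the same three sessions.

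Between visits the arms differ. For app users the protocol describes:
- daily clinical and research moderation of the forum, and peer moderation on weekdays;
- a keyword alert on posts;
- a watch for deterioration by the research team and moderators (Criteria for discontinuing {11b});
- a weekly call, described as "a short conversation about their progress, any technical issues experienced, and to answer any of their questions".

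For controls, section {18b} says: "Participants in control will be contacted 2 weeks before each assessment to schedule the next assessment". A text reminder follows the day before the visit.

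**The concern.** The outcome window and the stated active-assessment window differ within one paragraph, and the harms section describes a third arrangement, screening at visits. A reader cannot tell which events count towards the safety result after app use ends, or in controls at any time between visits.

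This matters because the conclusion turns on whether any event is reported. Under a zero-event rule, the way events are looked for largely decides the answer. Someone who self-harms after the app period and has recovered by the 3-month visit is counted only if the visit asks about the interval. During app use, more contacts can bring an event to light in one arm than in the other. A raw comparison would then mix a difference in risk with a difference in looking.

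**Working it through.** The protocol gives no event rate and no precision target for safety, so there is no figure to reproduce. The check sets the sections side by side, then sizes the time under each kind of monitoring.

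**Where events can be found**

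| Period | Peer Tree | Control |
|---|---|---|
| Randomisation to onboarding | none described | no such wait |
| App use (6–8 weeks); 6-week wait in controls | forum moderation, keyword alert, deterioration watch, weekly call | scheduling contact and reminder |
| Post-intervention visit | risk screen | risk screen |
| 3 months to follow-up | no clear monitoring described | scheduling contact and reminder |
| Follow-up visit | risk screen | risk screen |

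One entry is unsettled. Section {18b} speaks of weekly contact with the intervention arm for the length of the trial, while section {11c} limits it to the length of the intervention. Whichever is meant, the call is described in terms of progress, technical problems, questions and encouragement.

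**What the visit screen covers.** It addresses the same three areas as the safety definition. Two of the three event types are themselves defined as risk, so a risk screen fits them closely on the day. Self-harm is defined as something that happened, and a screen for present risk need not reveal a past episode. Nowhere does the article say that the screen asks about the interval since the last visit. The supplementary risk protocol, which might say so, is not shown.

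**Share of time under between-visit monitoring, app arm.** Inputs are app use of w = 6 to 8 weeks, and 3 months taken as 13 weeks (assumption). Onboarding wait L is not given and is set to 0.

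- share = w / (L + w + 13)
- w = 6: 6/19 = 0.316
- w = 8: 8/21 = 0.381

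Any wait L > 0 lowers the share. For controls the share is 0 of 6 + 13 = 19 weeks.

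**Illustration of comparability.** Assume a constant weekly event rate, complete capture during app use, and a visit screen that otherwise captures a share s of events since the last visit. The value of s is not in the protocol. Detected share is (w + 13s)/(w + 13) in Peer Tree and s in controls. For s = 0.25 and w = 6 this is 9.25/19 = 0.487 against 0.25.

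| s (assumed) | Peer Tree, w = 6 to 8 | Control | Apparent ratio with equal true risk |
|---|---|---|---|
| 0.25 | 49%–54% | 25% | 1.95–2.14 |
| 0.50 | 66%–69% | 50% | 1.32–1.38 |
| 0.75 | 83%–85% | 75% | 1.11–1.13 |
| 1.00 | 100% | 100% | 1.00 |

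The imbalance disappears only if the visit question recovers everything since the previous visit.

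**The case against.** The strongest reply is that safety does not rest on the one sentence about the intervention period. Both arms are screened at every assessment, including the 3-month visit. App users have daily moderation, and the deterioration watch is assigned to the research team as well as to forum moderators. The outcome counts only events caused by Peer Tree, so a between-arm rate is not the stated endpoint. The wording of screens and calls belongs in the supplementary risk protocol and moderator manual, which are not shown. The more intensive watch on app users would also tend to raise their count relative to controls, so it does not flatter the app.

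Most of this stands, and it rules out four stronger readings that a reader might infer:

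- **Events are sought only during app use.** The harms section contradicts this for both arms.
- **Detection rests on calls that carry no safety question.** The calls are not presented as the main detection route; moderation and the deterioration watch are described separately.
- **There is no comparator.** Controls receive the same visit screen. What limits a comparison is the attribution clause, together with unequal looking between visits.
- **The count is understated, with 62% to 68% of events missed.** Those percentages (13/21 and 13/19) are follow-up time. One good question at a visit can cover the whole preceding interval.

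The reply does not remove the mismatch of windows or the inequality between visits. Moderation and the keyword alert depend largely on forum posts, and section {11c} itself expects that some participants will not be using the forum. Attribution also does not make control data redundant: deciding whether an event was caused by the app is easier with background events collected in the same way.

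**Conclusion.** The point holds as a reconciliation and a cheap improvement. The Peer tree safety and harms sections must agree on the collection window. Between visits, described monitoring covers 32% to 38% of post-randomisation weeks in the app arm and none in controls, assuming 13 weeks for 3 months and no onboarding wait. Events that occur and resolve between visits may be missed in either arm, and totals that include forum- or call-detected events cannot be compared between arms.

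How many events would be lost cannot be determined, because it depends on what the visit screen asks about the preceding interval. Nor is the net direction known: incomplete capture lowers both counts, while closer watching raises the app arm's count relative to controls. The ratios above are illustrations under assumed capture.

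**What to change.** 1. State in Peer tree safety, and repeat in section {22}, that events are collected from randomisation to the 3-month follow-up visit in both arms.
2. At the post-intervention and follow-up visits, ask every participant the same scripted question about each listed event type since the previous visit, and record the date. Since randomisation takes place at the baseline session, this also covers any onboarding wait. The dates allow for intervals of different length in the two arms.
3. Report these answers by arm before anyone judges whether an event was caused by Peer Tree, then report the attributed count.
4. List events found only through the forum or calls separately, outside the between-arm comparison.

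This needs a short script at visits already scheduled and a minor amendment. It changes data collection only, not the handling of risk. Visits become slightly longer, and the event count may be higher and less favourable. Because Trial status says that data collection has begun, the report should state how many participants in each arm were asked the question at each visit.
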